#### *Outcome measures*

The primary outcome measure will be the Montgomery-Asberg Depression Rating Scale (MADRS) [28] total score at week 12. Ratings will be made on the basis of a semi-structured clinical interview at baseline and at every follow-up visit until week 12. The MADRS was chosen as the primary outcome measure as it has been demonstrated to be more precise in estimating changes in depression severity compared to other measures [29, 30]. However the HRSD remains a useful screening tool and the use of different assessment scales at screening and follow-up mitigates the risk of clinician bias whereby raters over-estimate symptom severity at screening stage to increase study recruitment. This can then mask the true treatment effect and may lead to an inflated placebo response.

Other outcomes recorded will include the 24-item Hamilton Rating Scale for Depression (HRSD-24) [25] which includes assessment of atypical depressive symptoms, the Clinical Global Impression (CGI) scale [31], an overall measure of illness severity, the 7-item

Generalized Anxiety Disorder scale (GAD-7) [32], a self-report measure of severity for generalised anxiety disorder and a modified Morisky measurement of medication adherence (MMAS-4) [33]. We will also assess changes in body mass index (BMI) from baseline to week 12. All scales have been validated for use in the Urdu language and have been used in previous studies in Pakistan [24]. Adverse effects will be monitored using a side effect assessment scale based on the product monograph of simvastatin.

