280 To compare response and remission rates between groups logistic regression will be used in  
281 which patients will be classified as in remission or not according to standard criteria on the  
282 MADRS scale. As there are multiple measures, p values will be adjusted for multiple  
283 comparisons using a correction based on controlling the family-wise error. Outcomes at  
284 timepoints other than 12 week follow-up will be considered exploratory and the main focus  
285 will be effect sizes (standardized regression coefficients).

286

287 To compare frequency of adverse events descriptive summaries will be presented by  
288 treatment group. Differences in the rates of AEs will be assessed by generalized linear mixed  
289 model with Poission or negative binomial distribution will be used given sufficient numbers  
290 of events, where time, treatment group and their interaction are fixed effects with subjects as  
291 random effects. Alternatively, simple count models will be used at each timepoint given the  
292 limited sample size and complexity of GLMM models.

293

294 It is likely there will be some drop-out of participants from the trial. Baseline predictors of  
295 missingness can be identified using logistic regression with the outcome (missing or not).  
296 Mixed effect models fitted through maximum likelihood can use all available information in  
297 the data potentially avoiding removal of dropout subjects from the analysis. Moreover, by  
298 including baseline predictors of missingness in the statistical models, the analysis may

assume the data to be missing at random (MAR). Diagnostic analysis will be conducted through checking residuals for outliers, influential data points and normality. If outliers or influential points are found a sensitivity analysis will be conducted after removing such points to see if the main findings change.

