The exploratory hypothesis that baseline lipid/CRP levels will affect response to simvastatin will be tested by adding the baseline lipid/CRP to a model for the primary outcome at 12 weeks, adjusted for baseline and including a treatment group by baseline lipid/CRP. The lipid/CRP level will be considered moderators if interaction with treatment group is significant (at significance level of 0.05, using bootstrapping for inference and construction of confidence intervals). If this is the case, exploratory plots that look at the group effect at different levels of the moderators will be used to study the nature of the moderation.

In order to test the hypothesis that changes in peripheral levels of lipids/CRP will be a mediator in the path between treatment and change in MADRS scores, an initial descriptive analysis will be conducted to look at the bivariate association between treatment group and change in lipid/CRP levels, and between change in lipid/CRP (at 4 and 12 weeks) and change in MADRS scores. A mediation model will then be fitted to the data that joint models the effects of treatment on the change in lipid/CRP at 4 weeks and MADRS at 12 weeks. The mediation effect is tested by the proportion of the total effect from treatment group to change in MADRS that goes through change in lipid/CRP. This model will be fitted in Lavaan in R or Mplus 7.11[35] and the indirect effect estimated through bootstrap resampling. Given the sample size, note the effect sizes for the indirect mediation pathway would need to be relatively large [36].

323

324 *Safety Monitoring*

325 Adverse events monitoring from the time informed consent is obtained until follow-up at 12  
326 weeks (using the side effect assessment scale). Laboratory parameters including total serum  
327 cholesterol, LDL, HDL, triglyceride, AST, ALT, LDH and CPK will be checked by the study  
328 physician before patient entry into the trial, and if there are any safety issues for which the  
329 patient should not be started on study medication, he/she will not be included to the study.

330

331 *Study coordination*

332 Local investigators will chair a weekly meeting with research assistants to help coordinate the  
333 study. The chief investigator will hold meetings with the research team every two weeks via  
334 Skype.

335

336 *Data protection and confidentiality*

337 For data security, consent forms and paper copies of assessment tools having any identifying  

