**Table 1: Assessment Schedule**

| Assessment                                  | Baseline | Week 2 | Week 4 | Week 8 | Week 12 | Ad hoc |
|---------------------------------------------|----------|--------|--------|--------|---------|--------|
| Medical Confirmation of Eligibility, SCID-5 | ✓        |        |        |        |         |        |
| Randomisation                               | ✓        |        |        |        |         |        |
| MADRS                                       | ✓        | ✓      | ✓      | ✓      | ✓       |        |
| HRSD-24                                     | ✓        | ✓      | ✓      | ✓      | ✓       |        |
| CGI                                         | ✓        | ✓      | ✓      | ✓      | ✓       |        |
| GAD-7                                       | ✓        | ✓      | ✓      | ✓      | ✓       |        |
| MMAS-4                                      | ✓        | ✓      | ✓      | ✓      | ✓       |        |
| Simvastatin dispensed                       | ✓        | ✓      | ✓      | ✓      | ✓       |        |
| TAU/Concomitant medication                  | ✓        | ✓      | ✓      | ✓      | ✓       |        |
| Adverse Effects Scale                       |          | ✓      | ✓      | ✓      | ✓       | ✓      |
| Basic clinical & psychiatric information    | ✓        |        |        |        |         |        |
| BMI                                         | ✓        | ✓      | ✓      | ✓      | ✓       |        |
| Biomarkers (CRP, lipids)                    | ✓        |        | ✓      |        | ✓       |        |

|                   |  |  |  |  |  |   |
|-------------------|--|--|--|--|--|---|
| Telephone contact |  |  |  |  |  | ✓ |
|-------------------|--|--|--|--|--|---|

613  
614  
615  
616  
617

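### The side-effect scale has no baseline rating although adverse events are monitored from consent, so existing complaints may be hard to tell from treatment-emergent ones

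*Protocol*

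**What the plan says.** **Safety Monitoring** gives the window and the instrument in one sentence, which opens "Adverse events monitoring from the time informed consent is obtained until follow-up at 12" and continues "weeks (using the side effect assessment scale".

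**Outcome measures** introduces the instrument: "Adverse effects will be monitored using a side effect" assessment scale, drawn from simvastatin's product monograph. It does not list the items, ask when a symptom began, or say how a symptom is attributed.

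**Table 1** has a row "Adverse Effects Scale". Its baseline cell is blank, and it is ticked at weeks 2, 4, 8, 12 and ad hoc. The other repeated rating scales (MADRS, HRSD-24, CGI, GAD-7, MMAS-4) all carry a baseline tick, as does BMI. A separate row, "Basic clinical & psychiatric information", is ticked at baseline only, and its content is not described.

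**Statistical Analysis** puts descriptive summaries by group first. It then states "Differences in the rates of AEs will be assessed by generalized linear mixed" model with a Poisson or negative binomial distribution, given enough events. The specification reads "of events, where time, treatment group and their interaction are fixed effects with subjects as" random effects. The fallback begins "Alternatively, simple count models will be used at each timepoint given the" limited sample size. Neither version has a baseline symptom term.

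**The concern.** Participants are not symptom-free when they enter. The Screening section requires a current antidepressant, and the Methods section says usual treatment may also include mood stabilisers and antipsychotics. Some overlap between their existing complaints and a checklist built from a drug monograph is a reasonable expectation, although the items are not shown.

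Without a pre-dose rating on the same scale, a complaint recorded at week 2 may be new, worse or unchanged, and the scheduled scale data alone cannot show which. Two consequences are possible: higher reported rates in both arms, and a comparison between arms pulled towards no difference. The second is the less comfortable direction for a safety comparison.

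The gap matters more here because the scale is the only structured on-treatment safety measure the protocol describes. The hepatic enzymes, LDH and CPK are described only before entry, and Table 1's one laboratory row covers CRP and lipids.

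**Working it through.** **Step 1. Text against schedule.**

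| Place | Start of coverage | Scheduled ratings on the scale |
|---|---|---|
| Safety Monitoring | Consent | Not listed; scale named as the instrument |
| Table 1 | Week 2 | Weeks 2, 4, 8, 12, plus ad hoc |

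The ad hoc tick allows the scale to be used for an event between consent and week 2. It does not give every participant a pre-dose rating.

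**Step 2. Can the analysis make up for it?** The model contains time, group, their interaction and a subject effect. The subject effect handles correlation among a person's repeated counts. It cannot split a person's level into existing and emergent parts, because no observation precedes dosing. The count models at each timepoint have the same limit. MADRS and the secondary outcomes, by contrast, are adjusted for baseline.

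**Step 3. Illustrative size.** The protocol states no adverse-event figure, so there is none to reproduce. The inputs *b* and *q* below are assumptions; only the 75 per arm comes from the protocol.

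- *b*: proportion with a listed symptom before dosing, the same in both arms on average through randomisation.
- *q*: proportion of the rest who develop it.
- Every existing symptom persists to follow-up and is counted. This is a worst case.

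Observed rate = *b* + (1 − *b*) × *q*. With *q* = 0.10:

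- *b* = 0.20: 0.20 + 0.80 × 0.10 = 0.28
- *b* = 0.40: 0.40 + 0.60 × 0.10 = 0.46

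The true emergent proportion among those free of the symptom is 0.10 in both cases.

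**Step 4. Illustrative dilution.** Take *q* = 0.10 in one arm and 0.20 in the other, with *n* = 75 per arm and two-sided 5%. Power by the normal approximation is

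Φ{ [ (p₁ − p₀) − 1.96 √(2p̄(1 − p̄)/n) ] / √( [p₀(1 − p₀) + p₁(1 − p₁)]/n ) }, where p̄ is the mean of p₀ and p₁.

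| *b* | p₀ | p₁ | Risk difference | Risk ratio | Power |
|---|---|---|---|---|---|
| 0 | 0.10 | 0.20 | 0.10 | 2.00 | 0.40 |
| 0.2 | 0.28 | 0.36 | 0.08 | 1.29 | 0.18 |
| 0.3 | 0.37 | 0.44 | 0.07 | 1.19 | 0.14 |
| 0.4 | 0.46 | 0.52 | 0.06 | 1.13 | 0.11 |

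The contrast shrinks as background prevalence rises. It does not change sign.

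**The case against.** **Surveillance window versus visit schedule.** Safety Monitoring can be read as the period under surveillance and Table 1 as the planned administrations. With an ad hoc column and ad hoc telephone contact, the two are not strictly incompatible. This stands in part: the wording is reconcilable, but no reading yields a pre-dose rating for everyone.

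**Existing symptoms need not be counted.** A reader might infer that pre-existing symptoms will be recorded as adverse effects in both arms. The protocol does not say so. No rule turns each endorsed item into an adverse event, raters may ask about onset, and some clinical information is collected at baseline. Operational definitions are left to a manual, and the counting rule may sit there or in the SAP, neither of which is shown. This stands, and the supportable word is *may*. Even so, a later document can define new or worse but cannot supply a rating that was never taken, and asking about onset at week 2 relies on recall.

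**The precision gain cannot be sized.** A reader might expect baseline adjustment to cut variance by *r*², or 25–36% for correlations of 0.5–0.6. That is a linear-model result with assumed correlations. It does not carry over directly to Poisson or negative binomial counts, so it is not claimed here.

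**Limited consequence.** No adverse-event comparison is powered: in the illustration, power is only 0.40 with no background at all. Modelling depends on having enough events. This stands and limits how much weight the point should bear.

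**Conclusion.** The point holds as a gap in scheduled data collection. The text ties adverse-event monitoring from consent to the scale, Table 1 plans no baseline rating on it, and the analysis has no baseline term. Existing complaints may therefore be indistinguishable from treatment-emergent ones. If they are counted, both arms' rates rise and the comparison is diluted. Randomisation means there is no systematic tilt towards either arm.

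The size is not known. The 28–46% range and the fall in risk ratio from 2.00 to 1.29 at 20% background, or 1.13 at 40%, rest on assumed prevalence and onset, full persistence and full counting. They show how the effect works and are not a forecast.

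The point concerns safety data only. The primary MADRS comparison and the planned 150 participants are untouched. It is a cheap improvement that should be made before enrolment, because a missing pre-dose rating cannot be recovered later.

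**What to change.** - In Table 1, add a baseline tick for the Adverse Effects Scale and state that it is completed before the first dose.
- In Safety Monitoring, say which ratings are scheduled, and that events between consent and week 2 are captured through the ad hoc route, so that text and table agree.
- Use the baseline rating to identify items that are new or worse than baseline in the adverse-event summaries and models. Entering the baseline score as a covariate is optional and can be settled in the SAP.

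The cost is one short checklist at a visit that already takes place, a few minutes per participant, with no extra visit.

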74   and supervision of researcher staff. This will include; ensuring research team members  
75   involved in the data collection and recording are centrally and consistently trained in the  
76   correct processes, having checklists for tasks involved in data collection, providing all  
77   researchers involved in assessments clear, written instructions through a Manual of  
78   Operations and Procedures (MOP) / Standard Operating Procedures (SOPs), which will detail  
79   operational data definitions, recruitment, screening, enrolment, randomization, follow-up  
80   procedures, data collection methods, data flow, case report forms (CRFs), and quality control  
81   procedures.

82

83   Participants will be randomised to receive either simvastatin and treatment as usual (TAU), or  
84   placebo and TAU for 12 weeks. All participants will provide written informed consent after  
85   reading the information in English and/or Urdu. Treatment as usual (TAU) will comprise of  
86   medication including antidepressants, mood stabilisers and antipsychotics and routine input  
87   from mental health services. There are little, if any provisions for psychosocial interventions  
88   to patients with depressive disorders in Pakistan. Simvastatin added to TAU will be 20mg  
89   taken once daily. This dose has been found to be safe and well tolerated as well as effective  
90   in reducing depressive symptoms in a population with moderate to severe depression [22].

91

92 The trial has been registered with Clinicaltrials.gov in (ClinicalTrials.gov identifier:  
93 NCT03435744).

94

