#### 95 *Sample Size*

96 We estimate a moderate effect size of 0.60 will be reported at week 12. Assuming a type-1  
97 error of 5%, we will need to follow up 120 patients across the two groups to achieve 90%  
98 power at Week 12. With an anticipated dropout rate of 20% by Week 12, we will randomise  
99 150 participants. An effect size of 0.4 or greater for difference in MADRS scores in  
100 randomised controlled trials of antidepressants versus placebo has been suggested as  
101 necessary to suggest clinical utility for an antidepressant used as monotherapy. A sample of  
102 120 participants is therefore powered to detect moderate to large effect sizes and trends  
103 towards significance in areas of smaller effect.

104

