#### *Exclusion Criteria*

Primary psychotic disorder or bipolar disorder; history of intolerance to statins or presence of any contraindication to statins; presence of any serious medical condition or neurological problem; presence of autoimmune or inflammatory disorder (e.g. systemic lupus

erythematous, rheumatoid arthritis and inflammatory bowel disease); alcohol or drug dependence; active suicidal ideation; pregnant or breast-feeding. Patients with a serum low density lipoprotein (LDL) level of <80 mg/dL at baseline are also excluded from the study as are patients with abnormal hepatic enzymes (Aspartate transaminase (AST) and Alanine transaminase (ALT)) or abnormal Lactate Dehydrogenase (LDH) or Creatinine Phosphokinase (CPK) values at baseline. Patients already on statin treatment will also be excluded.

The criteria for leaving the study are: (1) at the participant's request; (2) at the discretion of the responsible physician or trial investigator (e.g. an adverse event, poor compliance). Poor compliance is defined as either taking <75% of study medication between assessments points at baseline, week 2, 4, 8 and 12 or missing trial medications all together for  $\geq 7$  days in period (3) pregnancy.

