#### *Randomisation and Allocation Concealment*

Randomisation service will be provided by an independent statistical support service based in the UK. We will stratify randomization based on severity of depressive symptoms at baseline and study centre. Participants will be assigned to groups via random generation of allocation sequence, balanced across allocation group. Each participant will be assigned a unique study patient identification number once they have given informed consent and eligibility has been confirmed. The central trial pharmacist will prepare a 12-week package of treatment bearing the patient's name and ID number and send it to the site pharmacy. Thus, the site pharmacy will not know the treatment allocated to the patient. A study information leaflet will be given

to the participant, explaining that they are in a clinical trial and that in addition to TAU they are taking a placebo or simvastatin. This leaflet will also have the name of the local PI's.

Allocation will be masked from study investigators and co-investigators until participants have completed all follow-ups and the database is cleaned and locked. The trial pharmacist at the central pharmacy will keep the drug codes. There will be detailed protocols regarding maintenance of blindness for raters and governing unblinding procedures in case of emergency for pharmacists. To assess the integrity of blinding procedures, participants and independent raters will be asked to complete a conventional guess form asking whether they believe participants received simvastatin or placebo as a treatment after the final ratings have been completed.

If any participant develops side effects or suffers an emergency requiring drug unblinding, the responsible consultant and care team will be informed of the trial drug, probable side-effects and make a decision of participant continuation in the trial. Participant well being and safety will be crucial at all times and locally and internationally accepted Good Clinical Practice will be observed across the trial's governance procedures

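### AST, ALT, LDH and CPK bar entry but are never scheduled again on treatment; separately, the protocol counts two blood samples where its own schedule and mediation model need three

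*Protocol*

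**What the plan says.** **Entry.** Exclusion Criteria in the protocol rules out "patients with abnormal hepatic enzymes (Aspartate transaminase (AST) and Alanine transaminase (ALT)) or abnormal Lactate Dehydrogenase (LDH" and continues to CPK, all judged at baseline. Safety Monitoring has the same tests done at the same stage: "cholesterol, LDL, HDL, triglyceride, AST, ALT, LDH and CPK will be checked by the study" "physician before patient entry into the trial, and if there are any safety issues for which the" patient should not start study medication, that patient is not included. It names no later check.

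**On treatment.** Outcome measures states: "Adverse effects will be monitored using a side effect assessment scale based on the product monograph of simvastatin". Table 1 places that scale at weeks 2, 4, 8 and 12 and ad hoc. The only blood row in Table 1 is CRP and lipids, ticked at baseline, week 4 and week 12. Measurement of biomarkers names HDL, LDL and CRP as the analytes. The planned safety comparison in Statistical Analysis is of adverse events.

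**Number of samples.** Measurement of biomarkers asks for two blood samples, at baseline and week 12. Table 1 ticks three, and the mediation model in Statistical Analysis uses the change in lipids and CRP at week 4.

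**The concern.** The protocol treats four blood tests as important enough to keep a patient off the drug, and then does not schedule them while the drug is being taken, although blood is drawn on treatment for other purposes. A side-effect scale can pick up harm that a participant notices. It cannot pick up a rise in liver enzymes or CPK that causes no symptoms. At the end, the investigators could not set simvastatin beside placebo on the protocol's own safety tests.

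What is at stake is safety description, not the efficacy result. An analysis plan cannot supply it later, because results cannot be analysed if the assays were never scheduled.

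The sample count matters for a different reason. If sites follow the text of Measurement of biomarkers, no week-4 lipid or CRP value will exist and the mediation model cannot be fitted as described.

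**Working it through.** **Inputs, all from the protocol:** 75 participants per arm (Methods); 120 to be followed up, effect size 0.60, 90% power, 20% dropout, 150 randomised (Sample Size); two-sided alpha 0.05 (Statistical Analysis); visits and blood draws (Table 1, Measurement of biomarkers).

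**1. The plan's own figure.** A two-sample t-test with 60 per arm at effect size 0.60 and two-sided alpha 0.05 has power 90.3%. Dropout: 120 / 0.80 = 150. The stated sample size reproduces, and nothing below changes it.

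**2. What is scheduled, visit by visit.**

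| Visit | AST, ALT, LDH, CPK | Blood in Table 1 | Blood in Measurement of biomarkers |
|---|---|---|---|
| Before entry / baseline | yes | yes | yes |
| Week 2 | no | no | no |
| Week 4 | no | yes | no |
| Week 8 | no | no | no |
| Week 12 | no | yes | yes |

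Scheduled on-treatment enzyme or CPK values: 0 at 4 post-baseline visits. This count is the size of the gap. Week 12 is the one on-treatment visit at which both places agree that blood is drawn.

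**3. What a week-12 panel would add.** Taking 20% dropout in each arm, 75 × 0.80 = 60 participants per arm would be sampled. The documents give no rate of enzyme or CPK rise, so assume a range. The chance of seeing at least one case among 60 is 1 − (1 − p)^60:

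- p = 1%: 45%
- p = 2%: 70%
- p = 5%: 95%

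The panel would describe common rises and would settle nothing about rare ones. It also describes those still in the trial at week 12, so someone who left earlier because of an adverse event would not be in it.

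**4. Incidental findings.** Exclusion Criteria says only that a value is abnormal, without a cut-off. Assume that each test is flagged by chance in 0.5% to 2.5% of people and that the four tests are independent. The chance of at least one flag per person is 1 − (1 − q)^4:

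- q = 0.5%: 2.0%, and 60 × 0.020 = about 1 person per arm
- q = 2.5%: 9.6%, and 60 × 0.096 = about 6 people per arm

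So some mild abnormalities should be expected with no drug effect at all. They can be interpreted only by comparing the arms.

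**5. Sample count.** Measurement of biomarkers gives 2. Table 1 gives 3, and the mediation model cannot do without the third (week 4). Two places agree against one.

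**The case against.** The strongest reply is that the entry panel has a stated purpose, to decide who may start the drug, and that an entry test need not become an on-treatment measurement. Methods says of simvastatin 20 mg that it is "taken once daily. This dose has been found to be safe and well tolerated as well as effective". Exclusion Criteria removes patients with statin intolerance, contraindications or serious medical conditions. Treatment lasts 12 weeks in a trial described as pragmatic. No internal rule says that a panel done only before entry is wrong. This stands: on the enzymes, the protocol contradicts nothing, and the point is an improvement.

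A reader might go further than the text allows in three ways.

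- *That no enzyme or CPK result on drug could ever exist.* Adverse events are followed from consent to week 12, the scale can be used ad hoc, and a physician can withdraw a participant for an adverse event. Nothing bars a test prompted by symptoms, and the operating procedures are not shown. Only scheduled data are missing. Tests prompted by symptoms are selective, however, and would not give a comparison by arm.
- *That participants are exposed to a likely, unwatched harm.* The documents give no event rate and point the other way on tolerability.
- *That a rapid week-4 safety system is needed,* with urgent assays, action thresholds and by-arm tables for the DSMB. This rests on laboratory capacity in five cities that the protocol does not describe. The DSMB meets once a year and otherwise when necessary, so such tables would rarely help someone on a 12-week course.

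It may also be said that the blood-sample conflict is a separate matter. It is, and it lends no weight to the enzyme point.

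**Conclusion.** Two conclusions, both for consideration.

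1. **Enzymes and CPK: a cheap improvement.** The trial has no scheduled on-treatment AST, ALT, LDH or CPK data (0 of 4 post-baseline visits). It cannot report them by arm or show a symptom-free rise from scheduled data. This rests on reading Safety Monitoring and Table 1 as the full laboratory schedule; unseen operating procedures might add tests, but the protocol does not require any.
2. **Sample count: wrong as written.** Measurement of biomarkers conflicts with Table 1 and with the mediation model, and three samples is the reading that the analysis needs.

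The primary outcome, alpha and sample size are unaffected by either. The chances and counts in steps 3 and 4 of the working depend on assumed rates. They describe what the added panel could show and what it would cost, not how large the present gap is.

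**What to change.** - Add AST, ALT, LDH and CPK to the week-12 blood sample, and give them their own row in Table 1 (baseline and week 12).
- State that the results will be reported descriptively by arm after unblinding.
- Send marked abnormalities to the study physician and not to the raters, with the meaning of marked set in advance.
- Correct Measurement of biomarkers to three blood samples: baseline, week 4 and week 12.
- Running the enzyme panel at week 4 as well is optional.

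Cost: four routine assays per participant at one visit, one table row and a short amendment, with no added visit or draw at week 12. The protocol gives no assay price, sample volume or laboratory capacity, so the modest cost is a judgement. The downside is some incidental mild abnormalities to review, roughly 1 to 6 people per arm under the assumptions in step 4 of the working.
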